#### Secondary outcomes

*Low back pain*. At the time of patient recruitment the Visual Numeric Scale (VNS) [[50]] will be used to assess LBP intensity and daily activity limitations. A 30% increase in baseline LBP in the first postoperative month will be considered clinically significant. The VNS and the visual analogue scale have a good correlation and are equally sensitive to quantifying postoperative pain [51].

*Quality of life*. The validated Portuguese version of the EuroQol questionnaire (EQ-5D) will be used to assess the quality of life of colonized and non-colonized groups with and without Modic changes [52]. The EQ-5D is a self-administrated standardized instrument containing five items (mobility, self-care, usual activities, pain/discomfort, and anxiety/depression).

*Functionality*. The functionality of the participants will be quantified through the validated Portuguese version of the Oswestry Disability Index (ODI) for LBP [53].

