#### Inclusion criteria

The inclusion criteria for the study will be participants aged between 18 and 65 years; both sexes; complaint of low back pain lasting more than 3 months; magnetic resonance imaging findings of lumbar disc degeneration (LDD) performed less than 6 months before inclusion in the study; indication for open surgical treatment with isolated microdiscectomy or associated with lumbar arthrodesis; failure of conservative treatment for at least 6 weeks and/or progressive neurological deficit; agreement to follow all phases of the clinical investigation, having signed the informed consent form (ICF) for participation in the study.

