### Withdrawal of a study participant

A participant will be removed from the study in cases of ICF withdrawal, death, recruitment failure identification, loss of post-surgical follow-up, or the presentation of clinical symptoms of infection, intense pain, fever without other infectious *foci*, increased erythrocyte sedimentation rate and/or C-reactive protein, leukocytosis, imaging tests compatible with spondylodiscitis, or any other condition that leads to blinding interruption.

The reason and circumstances of each participant’s withdrawal from the study will be detailed. The data gathered until the patient is withdrawn from the study will be included in the final analysis.

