### Adverse effects

Failures related to surgical treatment, such as surgical wound infection, CSF leak, deep vein thrombosis, pain recurrence, or any other adverse events that may arise in the postoperative period, will be reported and considered in data analysis.

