### Questionnaires

Questionnaires on pain (VNS), functionality (ODI), and quality of life (EQ-5D) will be given at recruitment as well as at 1, 3, and 6 months postoperatively. A professional who is not involved in the study will collect all questionaires. Follow-up clinical visits will be carried out at 1, 3, and 6 months postoperatively, with acceptance deviation of 7, 14, and 21 days, respectively.

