## Statistical planning

### Sample size calculation

Considering the main outcome proposed, the identification of disc colonization by *C*. *acnes*, the minimum sample size (*n*) for the population of interest will be 96 participants, according to the calculation described by Medronho et al., [59] using a confidence interval of 95% and a maximum margin of error of 10%.

The ideal sample size for analysis of secondary outcomes will depend on the incidence of the main outcome. If it is too low, an increase in the number of patients included will be performed with the inclusion of more blocks of participants. In order to have a more accurate dimension, the sample size calculation will be revised as soon as we reach half of the initially planned sample size.

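### The only clinical-significance threshold for back pain is a 30% rise from baseline at month 1, which patients with high baseline pain cannot reach and for which no reason is given

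*Protocol article*

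**What the plan says.** Under Secondary outcomes, the protocol article measures low back pain with the Visual Numeric Scale (VNS). At recruitment the scale "will be used to assess LBP intensity and daily activity limitations"; its range is not stated. The same paragraph sets the threshold: "A 30% increase in baseline LBP in the first postoperative month will be considered clinically significant". No other clinical-significance threshold for pain appears in the article.

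The surrounding text matters for reading it:

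- Inclusion criteria: participants have a "complaint of low back pain lasting more than 3 months", an indication for open surgery, and "failure of conservative treatment for at least 6 weeks and/or progressive neurological deficit". No upper or lower limit on the baseline pain score is set.
- Questionnaires: pain, function and quality-of-life forms "will be given at recruitment as well as at 1, 3, and 6 months postoperatively".
- Adverse effects: the events to be reported and considered in the analysis are "Failures related to surgical treatment, such as surgical wound infection, CSF leak, deep vein thrombosis, pain recurrence" and others.

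**The concern.** Two features of the threshold stand out.

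**Direction.** Patients who are already symptomatic and selected for surgery would ordinarily be judged on how far pain falls. A threshold that recognises only a rise puts a patient with full relief and a patient with no change in the same class. The article does not say why worsening was chosen.

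**Attainability.** A relative rise on a bounded scale is easy from a low start and impossible from a high one. The label *clinically significant* then stands for different absolute changes in different patients, and for some it cannot apply at all.

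At stake is any comparison of colonized with non-colonized patients that uses this classification. If the two groups start from different pain levels, they differ in how many members can be classified as worse, whatever happens to their pain after surgery.

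**Working it through.** **The plan's own figure.** The only computed figure is the sample size: "the minimum sample size (*n*) for the population of interest will be 96 participants", from a 95% confidence level and a 10% margin. With p = 0.5 (assumed, the value that gives the largest n), n = 1.96² × 0.5 × 0.5 / 0.10² = 96.04, which reproduces 96. It concerns the primary outcome only. No sample size or power is attached to the pain threshold, so nothing below changes it.

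**Ceiling.** A 30% rise is attainable only if 1.3 × baseline ≤ maximum, that is, baseline ≤ maximum / 1.3 = 76.9% of the maximum. This holds for any bounded scale that starts at zero. On 0-10 the limit is 10 / 1.3 = 7.69; on 0-100 it is 76.9.

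**What the rule asks of each patient** (assumption: 0-10, whole points):

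| Baseline | 1.3 × baseline | Lowest qualifying score | Points needed |
|---|---|---|---|
| 1 | 1.3 | 2 | +1 |
| 2 | 2.6 | 3 | +1 |
| 3 | 3.9 | 4 | +1 |
| 4 | 5.2 | 6 | +2 |
| 5 | 6.5 | 7 | +2 |
| 6 | 7.8 | 8 | +2 |
| 7 | 9.1 | 10 | +3 |
| 8 | 10.4 | none | unattainable |
| 9 | 11.7 | none | unattainable |
| 10 | 13.0 | none | unattainable |

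**Share of patients with a baseline of 8 or more.** The article gives no baseline distribution. Assuming a normal distribution rounded to whole points and restricted to 0-10, the share (and the number out of 96) is:

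| Assumed mean | SD 1.5 | SD 2.0 | SD 2.5 |
|---|---|---|---|
| 5 | 4.8% (5) | 10.3% (10) | 14.9% (14) |
| 6 | 15.8% (15) | 21.7% (21) | 24.8% (24) |
| 7 | 36.3% (35) | 37.6% (36) | 37.0% (36) |
| 8 | 61.2% (59) | 55.1% (53) | 50.0% (48) |

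**How bias could arise.** This is an illustration, not a prediction. Suppose one group has baseline mean 7 and the other mean 6, both with SD 2, and that patients able to qualify do so equally often in both groups. The observed event rates then stand in the ratio (1 − 0.376) / (1 − 0.217) = 0.624 / 0.783 = 0.80. The group with more baseline pain shows about 20% fewer events from the ceiling alone. With equal baseline distributions the ratio is 1, and the cost is lost information only.

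**The opposite direction.** A 30% reduction means a score of at most 0.7 × baseline: 7.0 from 10, 6.3 from 9, 5.6 from 8, 0.7 from 1. It is reachable from every baseline above 0.

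**The case against.** The strongest reply is that worsening may be intended. This is an analytical study of disc colonization, not a trial of surgical efficacy. Its hypothesis links colonization to back pain, and it tracks pain recurrence as a failure of treatment. A marker of postoperative worsening fits that purpose. This stands: a reader might infer that the endpoint is inverted by mistake, but the article does not show that. It shows only that the choice is unexplained.

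The reply can also say that the threshold need not be the main pain analysis. The VNS is collected at four time points, and Statistical analysis methodology lists two-group tests and repeated-measures methods that could use the full scores. The statistical analysis plan is not shown and may settle how the threshold is used. This stands too. The month-1 restriction belongs to the threshold, and one cannot infer that the later scores go unused.

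Three other stronger readings lack support:

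- *The endpoint is nearly empty.* No event rate is given or can be derived, and under the assumptions above about 39% to 95% of patients could still qualify.
- *The hypothesis predicts colonization in the patients with most pain.* Hypotheses and objectives relates colonization to disc degeneration and back pain, but does not predict more of it at higher baseline scores. The comparison is therefore not shown to be biased.
- *Patients who worsen will be removed.* The withdrawal criteria list "the presentation of clinical symptoms of infection, intense pain, fever without other infectious" foci and other findings compatible with infection. Some patients with marked worsening might leave on that ground, but the text does not say how it will be applied, and data gathered up to withdrawal are kept.

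What the reply does not answer is the ceiling. The article itself fixes the direction, size and time of the threshold, and the arithmetic holds whichever purpose lies behind it.

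**Conclusion.** The point holds as a weakness in a secondary outcome that should be fixed. The threshold is stated without a reason, has no counterpart for improvement, and classifies patients partly by their starting score.

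The firm part is the ceiling at 77% of the maximum, which needs only a bounded scale starting at zero. The score-by-score table also assumes whole points on 0-10. The share affected, about 5% to 61%, rests on assumed baseline means of 5 to 8 with SDs of 1.5 to 2.5 and cannot be narrowed from the article. Bias between colonized and non-colonized patients is conditional on a baseline difference between them; without one, the loss is of information. The primary outcome and the sample size of 96 are unaffected.

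**What to change.** 1. Make the VNS as a continuous score, adjusted for its baseline value, at months 1, 3 and 6 the main pain analysis. Patients at every baseline then contribute, and all planned visits are used. State the range of the scale.
2. Before analysis, confirm whether *increase* was meant to be *reduction*. Choosing the direction after results are seen would be post hoc.
3. If reduction was meant, correct the word.
4. If worsening was meant, give the reason, define it as an absolute-point rise, and report how many participants have a baseline from which it is unattainable. The report is needed because an absolute rise also has a ceiling: on 0-10, a rise of k points cannot be reached from a baseline above 10 − k.

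The cost is a few sentences in the protocol or the analysis plan. The scores are already scheduled for collection, so no new data and no change in sample size are needed.

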### Host multiomic characteristics

Proteomic and metabolomic techniques will be used to examine disc and plasma samples. The comparison of the group of molecules found in disc and plasma samples may contribute to the quantitative and qualitative identification of profiles using peripheral blood that are associated with the presence of the pathogen in the intervertebral disc. After processing the multiomic raw data using proper bioinformatics tools, statistical techniques will be applied to analyze them against the clinical–radiological and microbiological profiles of the participants. We expect to provide a molecular signature relating the presence of *C*. *acnes*, LDD and LBP.

### Adverse effects

Failures related to surgical treatment, such as surgical wound infection, CSF leak, deep vein thrombosis, pain recurrence, or any other adverse events that may arise in the postoperative period, will be reported and considered in data analysis.

## Sampling

The Schedule of enrolment, Interventions, and assessments is shown in Fig 1. During anesthetic induction, intravenous antibiotic prophylaxis will be administered after patient admission to the operating room. Cefazolin at a dose of 1 g replicated every 4 h for the duration of the surgery will be used as an antimicrobial drug. The antibiotic prophylaxis regimen will end with skin closure and will not be extended for additional postoperative time (Fig 1).

**Fig 1 pone.0271773.g001:**
[figure not shown]
Flowchart showing all stages of the study.

The clinical specimens collected will be:

Peripheral blood. A 10 mL aliquot will be obtained 30 min after the infusion of surgical antibiotic prophylaxis through upper limb venoclysis. This sample will be placed in a tube containing clot activator for further separation of the serum, which, in turn, will be stored at −80°C for further analysis.Skin swab. After skin asepsis with 2% chlorhexidine gluconate degerming solution and 0.5% chlorhexidine gluconate alcoholic solution, a swab will be collected from the region where the surgical incision will be performed.Intervertebral disc. Five fragments will be collected at each level approached during surgery. A set of sterile surgical tweezers will be used exclusively for collection, one for each tissue fragment collected. The forceps with tissue fragment will be given to a member of the laboratory who will monitor the procedure inside the operating room immediately after collection. Each fragment will be placed in a vial containing thioglycolate broth (Merck^®^, Brazil) and 20 glass beads. The vials will be labeled with the initials of the study participants and the type of clinical specimen. After collection, the vials containing the clinical specimens will be kept at room temperature (18°C to 22°C) and transported in a specific case to the laboratory within a maximum period of 2 h.Muscle–ligament tissue. Before obtaining the LIVD fragments, five fragments of muscle–ligament tissue adjacent to the collected disc will be collected. The same collection and initial cooling precautions used for the disc fragments will be followed when collecting the adjacent tissue.

### Laboratory analysis

#### Cultures

The skin swabs will be opened only in a laboratory setting. Samples will be seeded on blood agar plates (5% defibrinated sheep blood; blood agar base, 40 g/L; agar, 5 g/L) and anaerobic blood agar (5% defibrinated sheep blood; blood agar base, 40 g/L; agar, 5 g/L; hemin, 10 mL/L; menadione, 5 drops/L. After sowing in solid media, the swab will be inoculated in thioglycolate medium, where it will remain for 14 days. One of the plates will be incubated in a capnophilic atmosphere (5% to 10% CO_2_), while the other will be incubated in strict anaerobiosis (atmosphere containing 10% CO_2_,10% H_2_, and 80% N_2_) using an anaerobic chamber or Glove Box (Coy Labs^®^, USA).

The plates will be read after 24 h of incubation and, in case of growth, the colonies will be identified. In the absence of growth, they will be incubated again, and a new reading will be performed after 72 h. The thioglycolate vials containing skin swabs will be kept in a bacteriological incubator (35°C to 37°C) for 14 days. In a laboratory setting, the tubes containing disc fragments and muscle–ligament tissue will undergo vortexing (Even EVX2800-BI^®^, Brazil) for 15 s. All tubes will be kept in a bacteriological incubator (35°C to 37°C) and, after 24 h, the first subculture will be carried out using a 100 μL bacteriological loop. An aliquot of the thioglycolate will be taken and plated on blood agar and anaerobic blood agar. The first plate will be incubated in a capnophilic atmosphere and the second in strict anaerobiosis using an anaerobic chamber or Glove Box (Coy Labs^®^, USA). The plates will be read after 24 h and the colonies will be identified in case of growth. In the absence of growth, they will be incubated again, and a new reading will be performed after 72 h. The same procedure will be used for all thioglycolate vials (totaling six vials for each level approached). Thioglycolate tubes containing the clinical specimens will be kept in an oven for 14 days. Subcultures will be carried out after 72 h and always every 3 days, with the last subculture being carried out on the 14^th^ day of incubation in the same solid culture medium and atmospheres used in the first 24 h.

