Aware of this reality, Astur et al. proposed a protocol for a cohort study to identify *C*. *acnes* from intervertebral discs [25]. Although valid, the initiative has two significant limitations that should be highlighted. First, after collecting clinical specimens, their immediate inoculation in a liquid medium is not foreseen in the operating room, which increases the contact time of the samples with the aerobic environment and reduces the chances of microorganism recovery even with culture-specific techniques. Second, the authors also highlight sonication (ultrasound waves to release bacteria from the biofilm of surgical prostheses) of specimens for subsequent inoculation in automated blood culture vials; however, this technique was originally described for pathogen recovery from orthopedic prostheses rather than biological tissue [26] and, because the sonication parameters used are not clear (time, power, and frequency), the reproduction of results by other authors and the validation of this protocol is compromised.

Specific microbiological identification techniques, such as immediate inoculation of specimens in liquid culture medium while still in the operating room, vortex for sessile cell recovery, incubation time extension in an anaerobic atmosphere with replication every 72 h, and the use of Matrix-Assisted Laser Desorption Ionization Time of Flight Mass spectrometry—MALDI-TOF MS (Bruker Coorporation), and multiplex-touchdown PCR are strategies that assure reliable results regarding the presence of bacteria in intervertebral discs [27, 28], but they do not explain the pathways through which these microorganisms would participate in LDD and/or LBP.

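### The 72 h plate reading is scheduled only when nothing has grown at 24 h, so *C. acnes* appearing later on a plate with other growth can be missed

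*Protocol article*

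**What the plan says.** Laboratory analysis, Cultures, gives the reading rule twice.

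- Skin-swab plates: "The plates will be read after 24 h of incubation and, in case of growth, the colonies will be identified".
- Plates subcultured from the disc and muscle–ligament vials: "The plates will be read after 24 h and the colonies will be identified in case of growth".
- Both are followed by the same sentence: "In the absence of growth, they will be incubated again, and a new reading will be performed after 72 h".

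The rule for vials is then extended: "The same procedure will be used for all thioglycolate vials (totaling six vials for each level approached". Each subculture produces two plates: "The first plate will be incubated in a capnophilic atmosphere and the second in strict anaerobiosis using an anaerobic chamber or Glove Box". Repeats are scheduled as follows (the quote stops before the end of its sentence): "Subcultures will be carried out after 72 h and always every 3 days, with the last subculture being carried out on the 14^th^ day of". Media and atmospheres stay as for the first subculture. The reading rule is not restated for these later subcultures.

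Under Sampling, "Five fragments will be collected at each level approached during surgery", each placed in its own vial. Five muscle–ligament fragments and one post-antisepsis skin swab are also taken.

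The Introduction counts "incubation time extension in an anaerobic atmosphere with replication every 72 h" among the techniques that make findings in discs reliable.

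**The concern.** The second reading can only be there to catch organisms not visible at 24 h. Making it depend on a clean first reading withdraws it from specimens that also contain a faster-growing organism.

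Three uses of the data depend on it:

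- **Primary outcome.** A positive culture comes first, and mass spectrometry and PCR only confirm it (Primary outcome). PCR is applied to organisms already isolated (Genotypic characterization), so it is not a culture-independent check. A missed *C. acnes* lowers the primary proportion.
- **Contamination objective.** The swab and muscle–ligament plates follow the same rule, so *C. acnes* can also go unseen in the specimens against which a positive disc is judged.
- **Group labels.** Colonization status defines the groups for Modic type 1 frequency, and isolation of *C. acnes* defines them for metabolomics. A missed positive disc moves into the comparison group.

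**Working it through.** **Step 1: the protocol's own figure.** Sample size calculation gives 96 participants for 95% confidence and a 10-point margin. With an assumed proportion of 0.5 (none is stated), n = 1.96² × 0.5 × 0.5 / 0.10² = 96.04, which reproduces it. That margin covers sampling error only, not missed positives.

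**Step 2: what the rule does to one mixed vial.** If the 72 h in the subculture schedule is counted from inoculation, subcultures fall on about days 1, 3, 6, 9, 12 and 14. All draw on the same broth and use the same media. An organism that persists in the broth and shows at 24 h on the anaerobic plate would prevent the second reading of that plate each time. If it does not grow anaerobically and the rule is applied plate by plate, the anaerobic plate stays clear and gets its second reading. The text does not say whether the rule works per plate or per pair.

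**Step 3: loss per disc.** Let c be the share of *C. acnes*-positive vials that also hold an organism masking it in this way. The documents give no value, so c is an assumption. With k positive vials, masked independently, and one positive vial sufficient, the disc is missed only if all k are masked: probability c^k.

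| c (assumed) | k = 1 | k = 2 | k = 3 | k = 5 |
|---|---|---|---|---|
| 5% | 5% | 0.25% | 0.01% | below 0.01% |
| 20% | 20% | 4% | 0.8% | 0.03% |
| 50% | 50% | 25% | 12.5% | 3.1% |

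The single swab has k = 1, so its loss is c. If masking clusters within a patient, the loss for k of 2 or more lies above c^k but cannot exceed c. I give no figure for muscle–ligament tissue: five disc and five muscle–ligament fragments make ten, while Cultures counts six vials per level, so the number of control vials is unclear.

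**Step 4: effect on the primary proportion.** If m is the share of truly colonized participants missed, the observed proportion is p(1 − m). Take p = 46% for illustration, the anaerobe-positive rate the Introduction quotes from one earlier study, and c = 20%:

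- every colonized participant has one positive vial, m = 20%: 0.46 × 0.80 = 36.8%, a loss of 9.2 points
- two positive vials, m = 4%: 0.46 × 0.96 = 44.2%, a loss of 1.8 points
- three positive vials, m = 0.8%: 0.46 × 0.992 = 45.6%, a loss of 0.4 points

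At p = 20% and m = 20%, the observed proportion is 16%.

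**The case against.** The strongest reply has four parts.

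1. **The article does not say that plates with growth are thrown away.** A reader might infer this, but the text says only that colonies are identified. The handling of such plates may be in a laboratory procedure not shown. This part stands. The article does, however, state when the second reading takes place, and a plate with growth is outside that condition. The point is therefore about a stated rule, not an omitted detail.
2. **Slow growth of *C. acnes* is not stated.** Correct. It is inferred from the second reading, the 14-day incubation and the Introduction's emphasis on extended incubation. If *C. acnes* were always visible at 24 h, the rule would cost nothing.
3. **The design has safeguards.** Five separate disc vials and two atmospheres limit the loss, and Step 3 shows how quickly it falls once two or more vials are positive. A reader might infer that *C. acnes* is hidden at every subculture. That needs an organism that persists and also grows anaerobically, and it needs the reading rule to carry over to subcultures for which it is not restated.
4. **Proteomics offers another route.** The thioglycolate sediment is searched against a *C. acnes* protein bank, which does not depend on plate readings. It does not define the primary outcome, so it does not repair the proportion.

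A reader might also infer that the error favours the study hypothesis, because masking in the controls would make a contaminated disc look truly colonized. The documents do not support a direction. They give no co-growth rate for any specimen type, the swab follows two chlorhexidine preparations, masking in discs works the other way, and no rule classifies contamination from the swab alone. Larger losses could be obtained by requiring two positive fragments per disc, but the protocol states no such requirement.

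**Conclusion.** The point holds in a limited form. As written, plates with other growth at 24 h have no scheduled later reading, and *C. acnes* appearing later on them can be missed. Repeat subcultures may not remedy this. The effect on the primary proportion can only be downward. The net direction for the contamination assessment cannot be determined.

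The size is unknown. It could be material if positive discs usually have a single positive vial and co-growth is common, and it is small when several vials are positive. The figures rest on an assumed c, independence between vials, one positive vial being enough, and *C. acnes* often not being visible at 24 h. This is a cheap improvement to ascertainment. It does not show that the primary result would be wrong, and the sample size is unaffected.

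**What to change.** In Cultures, replace the conditional sentence in both places with an unconditional rule covering disc, muscle–ligament and skin-swab plates:

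- read every plate at 24 h and again at 72 h regardless of growth at 24 h, and say that this applies at every subculture
- subculture each distinct colony type seen at either reading
- call a plate *C. acnes*-negative only after the 72 h reading

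The cost is more incubator space and reading time. No extra specimen or staff role is needed. The change removes the loss caused by the conditional reading, but it does not guarantee recovery from a heavily overgrown plate.
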